## Abstract

**Introduction:**

Worldwide, there is a high frequency of chronic non-specific low back pain (CNLBP), which is a significant public health concern. The etiology is complicated and diverse, and it includes a number of risk factors such as diminished stability and weak core muscles. Mawangdui-Guidance Qigong has been employed extensively to bolster the body in China for countless years. However, the effectiveness of treating CNLBP has not been assessed by a randomized controlled trial (RCT). In order to verify the results of the Mawangdui-Guidance Qigong Exercise and examine its biomechanical mechanism, we intend to perform a randomized controlled trial.

**Methods and analysis:**

Over the course of 4 weeks, 84 individuals with CNLBP will be randomly assigned to receive either Mawangdui-Guidance Qigong Exercise, motor control exercise, or medication (celecoxib). Electromyographic data, including muscle activation time, iEMGs, root mean square value (RMS) and median frequency (MF), will be the main outcomes. The Japanese Orthopedic Association (JOA) Score, the Mcgill Pain Questionnaire (MPQ), beta-endorphin, and substance P are examples of secondary outcomes. At the start of treatment and 4 weeks later, all outcomes will be evaluated. SPSS version 20.0 (SPSS Inc., Chicago, IL, USA) will be used for all of the analysis.

**Discussion:**

The prospective findings are anticipated to offer an alternative treatment for CNLBP and provide a possible explanation of the mechanism of Mawangdui-Guidance Qigong Exercise on CNLBP.

**Ethics and dissemination:**

The Sichuan Regional Ethics Review Committee on Traditional Chinese Medicine has given the study approval (Approval No. 2020KL-067). It has also registered at the website of China Clinical Trial Center Registration. The application adheres to the Declaration of Helsinki’s tenets (Version Edinburgh 2000). Peer-reviewed papers will be used to publicize the trial’s findings.

**Trial registration number:**

ClinicalTrials.gov, identifier ChiCTR2000041080.

## Strengths and weaknesses of this research

1.The purpose of this study protocol is to conduct the first-ever single-blinded, randomized controlled trial to assess the effectiveness and potential mechanism of Mawangdui-Guidance Qigong Exercise for CNLBP.2.Biological markers and EMG data are included in the primary and secondary outcomes. There has been no agreement achieved despite numerous EMG investigations that attempted to disclose the CNLBP with muscle activity sequence mechanism. Beta-endorphin levels and substance P, which are quick, safe, and effective markers to gauge pain relief will be tested.3.Participants are limited by ages between 20 and 39 for easily identification of specific chronic LBP or CNLBP, further researches on differences of various ages are needed.4.This is a single-center RCT with limited sample size, multi-center experiments can be conducted to get reproducible and stable results in the future.5.The treatment duration keeps 4 weeks without longer-term observation, we plan to conduct a follow-up at the 8th and 12th weeks by phone after the trial finished.

## Introduction

Pain between the costal margin and inferior gluteal fold is known as low back pain (LBP). Chronic non-specific low back pain (CNLBP) is defined as LBP for at least 12 weeks, which is not caused by a specific pathology such as a tumor, infection, fracture, structural deformity, radiculopathy, osteoporosis, inflammatory disorder, or cauda equina syndrome (Furlan et al., 2009). The literature reports a wide range of estimated prevalence rates for CNLBP, ranging from 4 to 14% (Parthan et al., 2006; van Tulder et al., 2006; Chou et al., 2007). One of the most prevalent musculoskeletal conditions in the world today is CNLBP (Maher et al., 2017). Effective therapies from drugs to surgery for CNLBP are widely used (Ma et al., 2019). NSAIDs, such as Celecoxib and other COX-2 inhibitors are frequently advised for the treatment of CNLBP (Birbara et al., 2003; Katz et al., 2003; Pallay et al., 2004; Airaksinen et al., 2006). The effectiveness of exercise therapy in CNLBP, including pilates, Tai Chi, yoga, and motor control exercise (MCE), has received greater attention in recent years (van Middelkoop et al., 2011; Holtzman and Beggs, 2013; Macedo et al., 2013; Eliks et al., 2019). For the treatment of persistent, nonspecific LBP, exercise therapy has been utilized extensively (Saragiotto et al., 2016).

Mawangdui-Guidance Qigong Exercise is an arising exercise therapy organized and created by the Fitness Qigong Management Center of the State General Administration of Sport of China (Fan, 2002). Traditional Chinese exercises, including Qigong and Tai Chi, are recommended to relieve pain intensity in patients with LBP (Zhang et al., 2019). Qigong may achieve the same efficacy as other exercise therapies in the treatment of CNLBP (Blödt et al., 2015). The pain intensity and back dysfunction are significantly regulated for people who practice Qigong (Phattharasupharerk et al., 2019), and it is safe in the treatment of musculoskeletal pain (Marks, 2019).

In order to assess internal and external postural interference in patients with LBP, the quick arm raise test and the falling ball test by surface electromyograph (sEMG) are frequently utilized (Hodges and Richardson, 1996; Tsao and Hodges, 2008; Jacobs et al., 2017; Xie and Wang, 2019; Larivière and Preuss, 2021; Yu et al., 2021). Although no consensus was established, numerous EMG studies attempted to shed light on the CNLBP with muscle activity sequence mechanism (Geisser et al., 2005; Marshall and Murphy, 2008; Falla and Hodges, 2017). The influence of adjusting posture on pain reduction and disability improvement may be observed by using EMG to examine the changes in muscle initiation time and iEMGs in patients with CNLBP (Yu et al., 2021). The management of spinal postural alignment and overall body balance are thought to depend mostly on the back muscles (Daggfeldt and Thorstensson, 2003; Christophy et al., 2012). The Chinese Association for the Study of Pain (Ma et al., 2019) advises sEMG y as an objective method of assessing the back muscles’ functionality (Akbari et al., 2015).

There is not enough solid evidence to support the high efficacy of Qigong when compared to other various nonoperative treatments. Mawangdui-Guidance Qigong Exercise has not been subjected to a randomized controlled trial (RCT) to determine the effectiveness in treating CNLBP. We strive to confirm the critical function in treating chronic CNLBP by contrasting Mawangdui-Guidance Qigong Exercise with MCE and medication.

## Methods and design

### Study design

This study is a randomized, single-blinded clinical trial to investigate the effectiveness of Mawangdui-Guidance Qigong Exercise for CNLBP. This study will be conducted at the Hospital of Chengdu University of Traditional Chinese Medicine (CDUTCM). For the duration of the 4-week course of therapy, 84 participants who meet the trial criteria will be assigned at random to the Mawangdui-Guidance Qigong Exercise group, the MCE group, or the medicine group. Participants in Qigong group and MCE group will receive different types of exercise therapies under the supervision of different professional coaches. Others in the medicine group will be given celecoxib orally on a regular basis. EMG data, including muscle activation time, iEMGs, root mean square value (RMS) and median frequency (MF), will be the main outcomes. The Japanese Orthopedic Association (JOA) Score, the Mcgill Pain Questionnaire (MPQ), beta-endorphin, and substance P will be the secondary outcomes. All outcomes will be evaluated at the start of treatment and 4 weeks later. We think Mawangdui-Guidance Qigong Exercise can produce an improvement in pain and lumbar function that is equal to or greater than what the other two groups can.

The study is approved by the Sichuan Regional Ethics Review Committee on Traditional Chinese Medicine (Approval No. 2020KL-067) and registered with China Clinical Trial Center Registration (ChiCTR2000041080). The implementation follows the principles of the Declaration of Helsinki (Version Edinburgh 2000). The SPIRIT guidelines and CONSORT flow diagram will be followed in this investigation. The whole study design will be illustrated as a flow chart in Figure 1 and the process timetable will be shown in Table 1.

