#### Secondary outcomes

The JOA Score (Oshima et al., 2020) and the McGill Pain Questionnaire (MPQ) (Main, 2016) are the secondary outcomes. JOA Score takes into account bladder function, daily activity, clinical indicators and subjective complaints, with the lowest score of 6 and the highest score of 29. Better functioning conditions are indicated by higher overall scores. MPQ is made up of 15 carefully chosen words, comprising 4 emotional and 11 sensory words. Each item is given a number from 0 to 3, with a higher score denotes a severer symptom (Choi et al., 2015). Biomarkers like substance P (Bhatia, 2015) and beta-endorphin (Choi and Lee, 2019) will also be tested.

All the primary and secondary outcomes will be assessed before and 1 week after treatment.

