### Statistical analysis

Test-retest reliability and content consistency reliability will be used to gauge the scale’s dependability (test-retest reliability). Cronbach’s coefficient is the most often used measure of internal consistency reliability. The better the homogeneity, the higher the Cronbach’s alpha coefficient. If the scale’s consistency is greater than 0.8, it is considered to be good, and if it is greater than 0.7, it is considered to be acceptable.

SPSS version 20.0 (SPSS Inc., Chicago, IL, USA) will be used for all of the analysis. The significance threshold will be set at 0.05, and the confidence interval will be 95%. The χ^2^ will be used to analyze categorical data. For continuous variables, mean ± SD will be recorded by using ANOVA test if they were normally distributed, or the median with interquartile range will be shown with Kruskal–Wallis H test. The Bonferroni correction and Tukey *post-hoc* test (for ANOVA) will be used to handle multiple comparisons (for Kruskal–Wallis). The Chi-square test will be used to verify the classification count data. Two-tailed test will be used in this study. The difference will be regarded as statistically significant when *P* < 0.05.

To handle missing data, we will evaluate the underlying cause, employ an imputation adjustment approach, and do a last observation carried forward analysis. Following the primary analysis, a sensitivity analysis will be carried out to determine the effect of missing data on the trial outcomes by contrasting the findings from the per-protocol analysis and the intention to treat analysis. Also planned are subgroup analysis by the center.

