## Discussion

The purpose of this study is to explore the effectiveness of Mawangdui-Guidance Qigong Exercise on CNLBP, and to further discuss the potential neuroelectrophysiology mechanism. Lumbar multifidus muscle has been proved crucial to the intersegmental stability of lumbar spine (Beimborn and Morrissey, 1988). Higher level of multifidus muscle activation observed in CNLBP patients is related to muscle spasm and the Pain Adaptation Model (Sherman, 1985; Ahern et al., 1988; Ansari et al., 2018). TrA primarily contributes to the dynamic stability of the lumbar spine by contracting the abdominal muscles to regulate various pain adaption models (van Dieën et al., 2003; Allison and Morris, 2008; da Silva et al., 2017). The data of lumbar multifidus muscle and TrA (Beneck et al., 2016; Shah et al., 2020) are usually collected using sEMG in the study of postural balance in patients with LBP. The relationship between neuromuscular control mechanisms and pain, however, is yet unclear.

Neurological system moderately activates the muscles at the proper time in the event of spinal injury, according to the “spinal stability model” (Panjabi, 1992). Feed-forward, feed-back, and voluntary control makes up of the basic central motor control modes of lumbar spinal stability muscles. According to visual, auditory, postural, and proprioceptive senses as well as feed-forward and feed-back control, the nervous system regulates the lumbar stability muscles to maintain lumbar stability or unconsciously protect the spine. The probable mechanism of Qigong may involve stretching and strengthening the core muscles in the waist. In patients with CNLBP, Mawangdui-Guidance Qigong Exercise, according to our hypothesis, preserves postural stability by altering the order of muscle activation.

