Since the pathophysiology of CNLBP is unknown, LBP is frequently included in discussions about CNLBP illness management (Maher et al., 2017). Inflammation may continue throughout the entire course of LBP (Vucetic and Svensson, 1996; Vroomen et al., 2002) and is a key component of both pain and spinal degenerative processes (Wuertz and Haglund, 2013; Risbud and Shapiro, 2014). Beta-endorphin and substance P are also advised as alternatives to inflammatory markers as indicators of how well a treatment is working for patients with LBP (Bhatia, 2015; Choi and Lee, 2019). We believe that Mawangdui-Guidance Qigong Exercise can achieve the same or even more improvement in pain and lumbar function than the other two groups.

Prescription of Mawangdui-Guidance Qigong Exercise revolve limb opening and closing, rotation flexion and extension, stretching, and bone stretching, based on meridian guidance. It is a popular kind of Traditional Chinese Medicine (TCM) rehabilitation exercise therapy recently for cardiovascular, metabolic, and musculoskeletal system diseases (Wang et al., 2014; Sun and Wang, 2015; Chen, 2016; Ding et al., 2019). Though it is beneficial to the changes in the cellular level of elderly women (Wang et al., 2016), generally speaking, application of guidance still focuses on the observation of the overall effect on the body. The current research should focus on the therapeutic impact mechanism of Mawangdui guidance.

Compared with younger people, people over the age of 40 have a higher incidence of degenerative diseases such as lumbar disc herniation (Brinjikji et al., 2015). It is difficult to prove that LBP in patients over 40 years old is not caused by the above-mentioned specific causes. The specificity and non-specificity of LBP can be easily identified in younger people. That is why we designed this RCT with participants limited by ages between 20 and 39. As a result, the current study could not clearly explain the differentiation between various ages, and future researches on the effectiveness of multiple ages are needed. Secondly, since the single-center design with limited sample size may restrict the credibility of this trial, multi-center experiments in the future may help in enhancing the reproducibility and stability of the research. In addition, the treatment duration keeps 4 weeks without longer-term observation, we plan to conduct a follow-up at the 8th and 12th weeks by phone after the trial finished.

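### The protocol expects Qigong to match or beat both active comparators on pain and function, but its two-sided difference tests, with no margin, cannot support the equality part

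*Protocol article*

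**What the plan says.** The protocol article states the expectation twice. Under Study design, the authors think Qigong can give "an improvement in pain and lumbar function that is equal to or greater than what the other two groups can". In the Discussion, they believe it "can achieve the same or even more improvement in pain and lumbar function than the other two groups". The other two groups are motor control exercise (MCE) and celecoxib, both active treatments.

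Pain and lumbar function are measured by the MPQ and the JOA score, both secondary outcomes. The primary outcomes are surface EMG measures, and the sample size is set on one of them, median frequency (MF). On the link between the two domains the Discussion says: "The relationship between neuromuscular control mechanisms and pain, however, is yet unclear".

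The Statistical analysis section fixes the inference. For continuous variables, "mean ± SD will be recorded by using ANOVA test if they were normally distributed", with Kruskal–Wallis otherwise and Tukey or Bonferroni for multiple comparisons. It adds "Two-tailed test will be used in this study" and "The significance threshold will be set at 0.05, and the confidence interval will be 95"%. Its only decision rule begins "The difference will be regarded as statistically significant when" and sets the limit at P < 0.05. The article closes by anticipating that contrasts with MCE and medication will offer an alternative treatment.

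**The concern.** Expecting a treatment to be at least as good as an active comparator is, in substance, a non-inferiority expectation. A two-sided difference test can support the *greater* half. It cannot support the *equal* half, because failing to reject no difference does not show that any difference is small. Without a margin, or a limit that the confidence interval must clear, no result under the printed rules can establish equality.

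There is no untreated arm, so presenting Qigong as an alternative treatment leans on how it compares with MCE and celecoxib. If the pairwise P values for MPQ and JOA are above 0.05, a reader who has seen the expectation twice could take them as confirming it. With arms of this size, that reading would often be wrong.

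**Working it through.** **Plan's own figures.** The article gives no SD, target difference or margin for MPQ or JOA, so there is no figure on this point to reproduce. Its only effect size, 0.44, belongs to the MF calculation. Read as a standardised mean difference in the stated two-sided 0.05 t-test with 95% power, it needs 136 per group, not 28. Read as Cohen's f in a three-group ANOVA, it gives 83 in total, or 84 in equal groups, without the dropout allowance. That discrepancy is a separate matter. It is relevant here only because 0.44 SD is one illustrative deficit among several.

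**Inputs**
- 28 per arm, 10% dropout, two-sided 0.05 and 95% confidence (Sample size, Allocation, Statistical analysis).
- Evaluable per arm: 28 × 0.9 = 25.2, taken as 25.
- True deficits of 0.3, 0.44 and 0.8 SD, and margins of 0.3, 0.5 and 0.8 SD: assumptions, given as ranges.

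**1. Precision.** Half-width of the 95% CI for a pairwise difference = t(0.975, 48) × √(2/25) = 2.011 × 0.283 = 0.57 SD. With all 28 per arm it is 2.005 × √(2/28) = 0.54 SD. A result centred on zero would still be compatible with Qigong being more than half an SD worse.

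**2. Chance of a non-significant result when Qigong is truly worse by d.** The test statistic is noncentral t with noncentrality d × √(n/2). At n = 25 that is d × 3.536. The unadjusted test uses 48 df; Tukey uses three groups and 72 df.

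| True deficit (SD) | Noncentrality | Unadjusted | Tukey |
|---|---|---|---|
| 0.3 | 1.06 | 82% | 90% |
| 0.44 | 1.56 | 67% | 79% |
| 0.57 | 2.02 | 49% | 64% |
| 0.8 | 2.83 | 21% | 33% |

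With 28 per arm, the 0.44 SD row becomes 63% and 76%. Unadjusted, non-significance is the likelier result only for deficits up to about 0.57 SD.

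**3. Power if non-inferiority were tested.** One-sided 0.025, true difference zero, noncentrality = margin × √(n/2), per comparison:

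| Assumed margin (SD) | 25 per arm | 28 per arm |
|---|---|---|
| 0.3 | 18% | 20% |
| 0.5 | 41% | 45% |
| 0.8 | 79% | 84% |

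Meeting the margin against both comparators is harder. By simulation with a shared Qigong arm, power at 25 per arm is 25% for 0.5 SD and 68% for 0.8 SD. For 80% power per comparison, 0.5 SD needs 63 evaluable per arm, or 63/0.9 = 70 recruited.

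**The case against.** The strongest reply is that the sentences are expectations (the authors think, or believe) and not a formal hypothesis. The only statement the article calls its hypothesis is mechanistic, about the order of muscle activation. The expectation also includes superiority, which the planned tests do address. All of this stands, so the point concerns a stated expectation on secondary outcomes and not a failed primary test.

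A reader might infer that the protocol will treat P ≥ 0.05 as equality. It does not say so: its rule covers only when a difference is significant, and the closing remark about an alternative treatment is not tied to a null result. Misreading is a risk that the text leaves open.

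A reader might also infer that non-significance is the likeliest result however much worse Qigong is. That fails for larger deficits, as at 0.8 SD above. If 0.44 is Cohen's f and one arm differs from the other two, the pairwise gap is 0.44 × 3/√2 = 0.93 SD. Non-significance at that gap is only about 10% (Tukey 19%).

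A margin could sit in an analysis plan that is not shown, so its absence alone is not held against the article. What remains is a conflict within the printed text: an expectation of equality beside an analysis and a sample size built only for differences.

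Finally, a reader might conclude that EMG should give way to pain and function as the primary outcome. A mechanistic primary outcome fits the stated aim, and nothing here requires changing it.

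**Conclusion.** The mismatch is real and limited in scope. The article expects equality or better on pain and function against two active treatments, and its analysis can show only a difference. A non-significant MPQ or JOA comparison would leave differences of roughly ±0.57 SD around the estimate open and could be misread as equality. A true deficit of 0.3 to 0.44 SD would go undetected in most such trials, and one of 0.8 SD in about a fifth (a third with Tukey).

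These figures rest on 25 evaluable per arm, approximately normal outcomes with a common SD, and deficits and margins chosen for illustration. The lack of a route to equality does not depend on them. The correction should be made because it governs the trial's clinical message, although the primary analysis is unaffected.

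**What to change.** 1. Reword the expectation in Study design and in the Discussion to say that the trial tests for differences (superiority) only.
2. Add to Statistical analysis that P ≥ 0.05 will not be reported as equal, the same or as effective.
3. Base any statement on pain and function, including the closing one about an alternative treatment, on the Qigong–MCE and Qigong–celecoxib differences in MPQ and JOA with 95% CIs.
4. Keep the EMG primary outcomes as they are.
5. If equality is to be claimed, fix a justified margin on MPQ and on JOA before unblinding. Require the CI to exclude it in both the intention-to-treat and per-protocol sets. Higher JOA is better and higher MPQ is worse, so the relevant limit is the lower one for JOA and the upper one for MPQ (Qigong minus comparator).

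Steps 1 to 4 cost only wording and need no further patients or measurements. Step 5 needs a clinical justification for each margin, and at this sample size the equality claim will probably be unavailable unless a wide margin can be defended.

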**FIGURE 1 F1:**
[figure not shown]
Flow chart of the whole study design.

**TABLE 1 T1:** Process timetable.

		Study period							
		Enrollment	Allocation	Post allocation			Close-out	Follow-up	
Timepoint	Week	−1	0	1	2	3	4	8	12
**Enrollment**									
Inclusion/exclusion criteria		√							
Informed consent		√							
Medical history		√		√	√	√	√		
Laboratory tests		√					√		
Muscle action time, EMG data		√					√		
JOA, MPQ		√					√		
Random allocation			√						
**Interventions**									
Mawangdui-Guidance Qigong Exercise				[figure not shown]					
MCE				[figure not shown]					
Celecoxib				[figure not shown]					
